## Methods and design

This is a multi-center randomized controlled trial (RCT) with two parallel arms and 1:1 allocation. A mixed analysis approach will be used. To assess the RCT’s effectiveness, a quantitative method will be used, while a qualitative approach will help understand subjective change processes considering cultural traits.

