### Participants

Patients will be recruited from six clinical centers from three different cities in Chile; four in Santiago, one in Valdivia, and one in Osorno. Ninety six people are expected to take part in the study, of which 48 will be patients diagnosed with a first episode of schizophrenia (divided into 24 trial and 24 controls) based on the following criteria: patients with a psychotic episode without a prior diagnostic of schizophrenia, patients diagnosed with schizophrenia for the first time, and/or patients who persist with the schizophrenia diagnosis after the first episode. Additionally considered is the participation of 48 patients under a high-risk mental state (divided into 24 trial and 24 controls) who meet the criteria of an Attenuated Psychosis Symptom Syndrome, including delusional beliefs, attenuated hallucinations, and disorganized speech with intact reality testing but of sufficient severity and/or frequency that it is not discounted or ignored [5]. Sample size was estimated considering a previous RCT for people with schizophrenia on both the MBI [20] and a cognitive remediation program [50]. The sample size was calculated by using the statistical program G*Power [51]. The sample required to detect statistically significant differences in the cognitive functioning for a two-tailed test of the proportions with an effect size of 0.80, an alpha of 0.05, and a power of 0.90 is 2 × 39. With an estimated 15–20% drop-out over 3 months, we decided to include 96 persons in the trial, 48 allocated in each intervention arm. The inclusion criteria are (1) patients diagnosed with a first episode of schizophrenia or in high-risk of psychosis, as applicable; (2) aged between 15 and 35 years; and (3) clinical stability defined by medical and psychometric criteria (e.g., PAANS). Exclusion criteria are (1) risk of suicide; (2) severe intellectual disability (mental retardation); (3) medical illness inconsistent with the intervention; and (4) substance abuse or dependence in the past 6 months. Figures 1 and 2 summarize the process of randomization, group allocation, and assessment. The SPIRIT checklist is available in Additional file 1.

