### Procedure

Participants, as defined above, will be randomly allocated (a simple randomized sampling will be used) to the trial or control group. Randomization to either trial or treatment as usual will be conducted by independent researchers using a stratified block randomization procedure with a computer-generated allocation sequence. Health experts who will implement the MBIs will be blind to this procedure and will not carry out the assessment.

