#### Control group

Participants will receive standard care for this illness (treatment as usual), in other words, pharmacology and psychosocial intervention under clinical guidelines (e.g., social skills workshop).

The assessment, application of neuropsychological tests (Measurement and Treatment Research to Improve Cognition in Schizophrenia (MATRICS) Battery), and self-reporting questionnaires will take place (1) before the workshop; (2) after the workshop; and (3) at follow-up 3 months after completing the workshop. Additionally, 4 weeks after completing the workshop, participants will be submitted to semi-structured interviews. The number of interviews will be defined based on the saturation of the concepts found in the qualitative methodology. Each interview will last approximately 20 minutes and will be performed by a member of the research team.

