### Data analysis

A mixed qualitative and quantitative analysis method will be used. Qualitative information will be collected by means of semi-structured interviews and assessed with the Grounded Theory. This data analysis approach is widely used in social sciences and was previously applied for the analysis of the subjective experience of patients with psychosis [26]. This methodology will analyze the patients’ subjective experience regarding the feasibility and contribution of this type of intervention in a local context. At the quantitative level, the hypothesis will be contrasted though a mixed designed ANOVA in order to consider both the impacts of the intervention (inter subjects) and time (intra-subject; pre, post, and follow-up measurements) in every variable assessed. The analysis will help prove the hypotheses regarding the efficiency of this intervention in both patient groups. If statistically significant differences are found between the trial and control groups at the beginning of the intervention, corrections will be conducted using an ANCOVA.

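### Baseline adjustment depends on a baseline significance test; adjusting every outcome for its pre-workshop score in all cases would fix the model in advance and gain precision at no cost

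*Protocol article*

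**What the plan says.** The design has "two parallel arms and 1:1 allocation" (Methods and design), and the Procedure section describes a "stratified block randomization procedure with a computer-generated allocation sequence". The Control group section schedules the cognitive battery and the questionnaires at "1) before the workshop; (2) after the workshop; and (3) at follow-up 3 months after completing the workshop", so a baseline value of every quantitative outcome is planned for everyone.

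The Data analysis section tests the hypotheses with a mixed-design ANOVA that has arm as the between-subject factor and "time (intra-subject; pre, post, and follow-up measurements) in every variable assessed" as the within-subject part. It then adds a rule that, if "statistically significant differences are found between the trial and control groups at the beginning of the intervention, corrections will be conducted using an ANCOVA". No other part of the article makes baseline adjustment unconditional. The article does not name the baseline variables to be tested, the level of that test or the covariate in the ANCOVA. It also does not say which ANOVA term (arm, or arm by time) carries the hypothesis.

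**The concern.** This is a stated decision rule, not a detail left for a fuller plan. Three things are wrong with it.

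- Under proper randomisation any baseline difference between arms is a chance finding. A significance test of it tests a hypothesis already known to be true.
- The model is chosen after looking at the data. A test at 0.05 will trigger the switch for about 1 variable in 20, and the other 19 stay with the default. Imbalances just short of significance do as much harm as those just past it, yet are treated differently.
- The pre-workshop score is likely to be the best predictor of the later score. Used as a covariate, it gives a more precise comparison than when it is only one level of the time factor.

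At stake are a model fixed in advance for the primary outcome and some power. The power matters most for effects below the planned 0.80 and for the separate conclusions the plan wants in each patient group.

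**Working it through.** **Inputs.**

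- From the Participants section: 48 per arm, of whom 24 per arm in each patient group; drop-out 15% to 20%; alpha 0.05; planned effect size 0.80. At 20% drop-out, 48 × 0.80 = 38.4, so 38 completers per arm. Within one patient group, 24 × 0.80 = 19.2 and 24 × 0.85 = 20.4, so about 20 per arm.
- Assumed, because the article gives no value: pre/post correlation r of 0.5 to 0.8, equal variances, and an illustrative effect of 0.5 SD beside the planned 0.80.

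The plan attaches no figure of its own to this rule, so there is none to reproduce.

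**1. How often the rule switches.** At 0.05 the baseline test fires in about 5% of trials per variable. If the seven MATRICS domains were tested separately and were independent (an assumption), at least one would fire in 1 − 0.95^7 = 0.30 of trials.

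**2. What passes as not significant.** With 38 per arm the largest such gap is t(0.975, 74) × √(2/38) = 1.993 × 0.229 = 0.457 SD. A change contrast subtracts the gap in full, although only r times the gap is expected to carry over. It therefore over-corrects by (1 − r) × gap. At 0.457 SD that is 0.23 SD for r = 0.5 and 0.09 SD for r = 0.8.

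**3. Type I error.** Simulating the two-step rule (change contrast, ANCOVA if the baseline test fires) gives an overall type I error of about 0.04 to 0.05, slightly conservative. Now restrict to trials with baseline p between 0.05 and 0.20. The mean absolute baseline z there is about 1.56. Given that value, the change statistic has mean (1 − r) × 1.56 / √(2(1 − r)) in absolute value and SD √((1 + r)/2):

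- r = 0.5: mean 0.78, SD 0.866; chance of exceeding ±1.96 is about 0.087
- r = 0.7: mean 0.60, SD 0.922; about 0.073
- r = 0.8: mean 0.49, SD 0.949; about 0.066

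Simulation agrees to within about half a percentage point (0.083, 0.072 and 0.068 at 39 per arm). ANCOVA stays at about 0.05 in the same trials.

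**4. Variance.** Relative to a single post score, the change score has variance 2(1 − r) and ANCOVA has 1 − r². The ratio is (1 + r)/2.

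**5. Power at 0.5 SD, 38 per arm (simulated, one later visit).**

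| Assumed r | ANCOVA variance ÷ change variance | Two-step rule | ANCOVA always |
|---|---|---|---|
| 0.5 | 0.75 | about 0.58 | about 0.69 |
| 0.7 | 0.85 | about 0.80 | about 0.85 |
| 0.8 | 0.90 | about 0.93 | about 0.95 |

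Normal approximation at r = 0.5: the change contrast has z = 0.5/0.229 = 2.18 and power Φ(2.18 − 1.96) = 0.59. ANCOVA has z = 2.18/√0.75 = 2.52 and power Φ(0.56) = 0.71. The t-based simulated values are slightly lower, as expected.

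**6. Power at the planned 0.80, r = 0.5.** Whole trial: about 0.94 against 0.98. Within one patient group, 20 per arm: about 0.70 against 0.80.

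**The case against.** The strongest reply is that the default is not a comparison of post scores alone. The pre score is already a level of the time factor, and the arm-by-time term works much like a change score. That stands. The baseline information is not thrown away, and any figure comparing ANCOVA with a post-only analysis describes something the plan does not propose. The loss is the smaller one in steps 4 and 5, and at r = 0.8 it is only about 2 points of power.

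A reader might infer that a data-driven choice of model must inflate the false-positive rate. It does not: averaged over randomisations the rule is conservative, and the unadjusted comparison is unbiased. The excess appears only conditional on a near-significant imbalance.

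A reader might also infer a much larger power loss. If the hypothesis were tested by the arm main effect averaged over all three occasions, the two-step rule would have power of only about 0.43 to 0.36 at 0.5 SD (r = 0.5 to 0.8), with type I error of 0.02 to 0.03. The article links the intervention effect to the between-subject factor, which permits that reading. But the hypotheses concern increase and persistence, which fit the interaction, and the article does not settle the matter. Most of that loss would come from the choice of term, not from the conditional rule.

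That different MATRICS domains would end up with different models is likewise a possibility. The article does not say whether the switch is made outcome by outcome.

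Finally, with the three-occasion interaction F-test the two-step rule reaches about 0.61, 0.84 and 0.96 at 0.5 SD for r = 0.5, 0.7 and 0.8. At r = 0.8 that matches single-visit ANCOVA. But that test draws on both later visits, so the like-for-like comparator is an ANCOVA of their mean. Its residual variance is (1 + r)/2 − r² = 0.50, 0.36 and 0.26, so the advantage of adjustment remains.

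**Conclusion.** The point holds as a matter of pre-specification and efficiency, and should be fixed. The rule lets a chance finding choose the model, leaves near-significant imbalances with about 7% to 9% conditional type I error, and gives up 10% to 25% of the variance of the treatment contrast for r between 0.8 and 0.5. In power this is about 2 to 11 points at 0.5 SD with 38 per arm. At the planned 0.80 it is about 4 points or less for the whole trial, and about 10 points within one patient group at r = 0.5.

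These sizes rest on an assumed correlation, a change-type contrast and an illustrative effect. The direction does not: ANCOVA is the more precise analysis at any correlation below 1. The article does not support a claim of overall false-positive inflation. The very low main-effect power cannot be taken as the plan's power unless the main effect is confirmed as the test.

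**What to change.** Delete the conditional sentence and do no significance testing of baseline differences. State instead that every quantitative outcome is analysed with its own pre-workshop score as a covariate, whatever imbalance is observed. This can be an ANCOVA, or a baseline-adjusted repeated-measures model of the post-workshop and 3-month scores. The arm effect should be estimated at post-workshop and at 3 months, which also settles which term answers the hypothesis.

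The cost is a rewrite of the quantitative part of the Data analysis section. It changes the stated default model, so it should be recorded as an amendment before outcome data are examined by arm. It needs no extra patients, visits or measurements.

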### Ethics

The research protocol follows the indications of the Singapore Statement on Research Integrity and has been approved by two ethics committees, namely Pontificia Universidad Católica de Chile and Universidad de Chile.

## Discussion

Schizophrenia is a chronic and severe mental health disorder. In Chile, it is a public health priority subject to integral treatment indications (pharmacological and psychosocial). There is abundant empirical evidence suggesting that MBIs are feasible and beneficial interventions for patients with schizophrenia. MBIs promote a more flexible relationship with the psychotic symptoms, with impacts on the patients self-awareness and own resources and not only on the shortcomings and limitations of having a chronic mental illness [7, 16, 29]. However, one of the elusive areas in targeting these psychotherapeutic treatments are cognitive impairments [7], while an adequate cognitive functioning has clear impacts on the psychological well-being of patients [64].

All the scientific evidence points to the need to study the relationship suggested in this project, i.e., to determine the impact of mindfulness on cognitive functions and the psychological well-being in people with schizophrenia. However, it is also worthwhile to include people with a high-risk mental state since this could provide insights in several areas, including (1) proving the efficacy of the MBI intervention for this group; (2) comparing the outcomes with those of patients with a first episode of schizophrenia (i.e., determine the scope of mindfulness according to the pathology level); and (3) allow subjective assessment of the mindfulness benefits according to patient experience when facing a reduction in psychological discomfort.

Thus, this study aims, on the one hand, to discuss different aspects that have not yet been addressed in the literature concerning MBIs applied in psychosis and, on the other, to confirm previous findings in other social and cultural contexts so as to improve the ecological soundness of this intervention [28]. In addition, the insights provided by self-reporting studies need to be improved through more accurate measurements such as neuropsychological tests.

Should the hypotheses suggested in this study be proven, this would add empirical evidence about the benefits and feasibility of MBIs for the psychotherapeutic treatment of patients with schizophrenia as well as of those with a high-risk mental state in reducing cognitive impairments in attention, working memory, and social cognition. The results would also increase the psychological well-being by empowering patients’ personal resources in the management of their own symptoms and psychotic experiences.

### Trial status

The research is presently in the sample recruitment phase and the workshops are expected to begin on November 15, 2016.

## Abbreviations

ACT: Acceptance and commitment therapy
MATRICS: Measurement and Treatment Research to Improve Cognition in Schizophrenia
MBI: Mindfulness-based intervention
RCT: Randomized controlled trial
